## Abstract

**Background:**

Guided self-help is a recommended first-step treatment for bulimia nervosa, binge eating disorder and atypical variants of these disorders. Further research is needed to compare guided self-help that is delivered face-to-face versus via email.

**Methods/Design:**

This clinical trial uses a randomised, controlled design to investigate the effectiveness of providing guided self-help either face-to-face or via e-mail, also using a delayed treatment control condition. At least 17 individuals are required per group, giving a minimum *N* of 51.

**Discussion:**

Symptom outcomes will be assessed and estimates of cost-effectiveness made. Results are proposed to be disseminated locally and internationally (through submission to conferences and peer-reviewed journals), and will hopefully inform local service provision. The trial has been approved by an ethics review board and was registered with ClinicalTrials.gov NCT01832792 on 9 April 2013.

## Background

Psychological therapy is the recommended treatment for eating disorders characterised by recurrent binge eating, with evidence-based self-help recommended as a first step of treatment
[1]. However, few studies have looked at how best to deliver this form of treatment, although outcomes and treatment adherence appear better when guidance is available from a healthcare professional (for example,
[2-4]), known as guided self-help or GSH. Furthermore, GSH has demonstrated particular cost-effectiveness, even when highly trained clinicians are used to administer the treatment
[5], and a number of other RCTs have supported the utility of cognitive behaviour therapy (CBT)-based self-help in the treatment of recurrent binge eating (see
[6] for a review). Typically this has been delivered face-to-face, but email-assisted therapy has been suggested as a helpful way of obtaining professional treatment without the need for face-to-face contact that is popular with patients and therapists
[7]. It is potentially less costly for health service providers, and may be more acceptable to certain subgroups of patients, for example, those who might not wish to attend face-to-face appointments
[8]. As eating disorders services often cover large populations, many individuals are required to make a long commute in order to attend appointments (for example,
[9]) and so treatments delivered over the Internet can circumvent many of the difficulties associated with this. Similarly, treatments that require less face-to-face contact can be perceived as more empowering (for example,
[10]) and are more cost-effective
[11].

Guided self-help also has potential beyond specialist eating disorders (ED) services. Högdahl *et al*.
[12] argue that bibliotherapy with email support has a similar content but is less costly than CBT and other Internet-based approaches. They argue that if effectiveness of such an approach can be established, it can be used in both specialist and non-specialist settings “due to minimal therapist training and low cost” (p. 38; see also
[13]). In the UK, for example, Improving Access to Psychological Therapies (IAPT) is a programme within the National Health Service (NHS) that supports delivery of recommended guidelines for anxiety and depression and has more recently expanded to treat other mental illnesses and long-term physical health conditions
[14]. Guided self-help significantly contributes to the interventions delivered by IAPT services
[14], although its application to eating disorders (and adults in particular) is not uniform. Given that EDs are associated with significant disability and cost-of-illness (for example,
[15]) - both areas targeted by the IAPT programme- the IAPT service may be well-placed to support the delivery of GSH to sufferers of some of these disorders (for example, see
[16]). Although limited data exist on the effectiveness of GSH in primary care, with significant early termination of treatment (for example,
[17]), rates of bulimia nervosa (BN) and binge eating disorder (BED) appear to be amongst the highest seen in affected groups. Only a minority of sufferers seek professional help and therefore being able to offer a variety of methods of delivering help may go further to reducing the devastating impact of these illnesses.

A previous randomised controlled trial (RCT)
[18] compared different forms of guidance and found that, although face-to-face guidance was superior to both telephone-based guidance and self-help with minimal guidance, telephone contact demonstrated promising results and may be useful when face-to-face contact proves difficult to arrange. A more recent RCT
[19] compared Internet-based GSH to a waiting list control for individuals with BN or BED. A self-help book
[20] was provided, and associated guidance took the form of email contact with a graduate psychology student. The treatment condition resulted in significant symptom improvement compared to a waiting list control. This was maintained at six-month follow-up and appeared comparable to results of face-to-face treatment in other studies, although no direct test of this was carried out. A recent study by Wagner *et al*.
[21] compared GSH and an Internet-based CBT program with therapist support in a sample of 155 females with BN or atypical BN. The two treatments were found to be comparableand effective in reducing ED symptoms at end-of-treatment and follow-up up to 18 months.

In addition to documented efficacy in favour of self-help, there is some emerging evidence that GSH for normal-weight binge eating disorders (that is, BN and BED) can be provided through methods other than face-to-face contact with a therapist (the term ‘therapist’ is preferred here; see below). There have, however, been few controlled studies directly assessing and comparing the effectiveness of different treatment modalities, and a recent review concluded that there exists a “lack of direct comparisons of Internet-based treatments to face-to-face treatments” for eating disorders [22, p. 549]. Only a small number of studies have compared different forms of guidance in GSH, and only one study has looked at email support compared to a control condition
[19]. One RCT comparing Internet-delivered CBT versus face-to-face group CBT
[22] is currently ongoing. Further research is needed to identify the efficacy and feasibility of different forms of guidance in order to develop cost-effective and beneficial treatments that can be adapted to patient need.

### Objectives and hypotheses of the RCT

The overall aim of the trial is to evaluate whether therapist support within GSH can be as effective when delivered via email as when delivered face-to-face. In this paper, we detail the design and methods of the current trial, and clarify the four main aims of the study. Specifically, these are to: (1) compare the effectiveness of face-to-face versus email GSH during treatment and at follow-up; (2) determine relative attrition and drop-out across the two treatments; (3) look at predictors of outcome in GSH (see below); and (4) determine the relative cost-effectiveness of these two treatments. The study also employs a waiting list control condition. The current paper describes the protocol on which the clinical trial is based, in line with suggested guidance (for example,
[23]).

In terms of the primary outcome measure, it is expected that both treatment conditions will be superior to the waiting list control condition (for example,
[4,18]). Although there is a limited amount of evidence in eating disorders, it is hypothesised that both treatments (face-to-face and email GSH) will be comparable in terms of effectiveness (for example,
[24]) in reducing binge eating frequency (see also
[21]). It is expected that similar results will be found with secondary outcome measures, drop-out and cost-effectiveness, although these variables have not yet been studied in detail in this way.

## Methods and design

### Study setting and trial design

The trial is a three-arm, individually randomised, controlled trial with two active treatments and a waiting list control. The study is being conducted within Oxford Health NHS Foundation Trust in the United Kingdom. The Eating Disorders Service covers a population of around 1.6 million adults and has three sites, each of which is recruiting participants as part of the trial. Participants are randomly assigned (using a random number generator) to one of three conditions: face-to-face GSH, email GSH or a waiting list control condition. Each condition lasts 12 weeks, and follow-up evaluations are conducted six months post-treatment. Ethical approval for this Trial was obtained from NRES Committee South Central-Oxford B, National Research Ethics Service, Reference: 13/SC/0217. The trial is registered with ClinicalTrials.gov, no. NCT01832792. Participants receive verbal and written information before consenting to the study, are asked to indicate written consent (after at least 24 hours to consider this), and are instructed of their right to withdraw at any time. The research was conducted in compliance with the Declaration of Helsinki and Good Clinical Practice (GCP) and will be reported in line with Consolidated Standards of Reporting Trials (CONSORT) guidance.

### Eligibility criteria

To be eligible for participation, individuals registered with a General Practitioner covered by Oxford Health NHS Foundation Trust must: (1) demonstrate regular binge eating (defined as either subjective or objective bulimic episodes) in the context of an eating disorder; and (2) be aged 17.5 or older. Participants are excluded from the trial if they reported any of the following: (1) body mass index (BMI) < 18.5; (2) recent rapid weight loss (defined at >1 kg/week); (3) any major medical condition that might interfere significantly with treatment; (4) current excessive drug or alcohol use; and (5) active and untreated psychosis or severe depression. Other contraindications to GSH (such as developmental disability that would impair the ability to participate in the treatment, or severe and complicated EDs) also represent exclusion criteria.

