### Primary and secondary outcomes

The primary outcome will be frequency of objective bulimic episodes, as assessed by the Eating Disorder Examination Questionnaire (EDE-Q) (see below). Comparisons will be made between pre-treatment, post-treatment and follow-up in the intervention groups. Secondary outcome measures include overall eating psychopathology, other ED behaviours, such as self-induced vomiting, psychological distress, self-esteem, functional impairment and healthcare usage, assessed by self-report (see below). Some of these variables (for example, severity of ED psychopathology) will be considered as predictors of outcome, as well as considered aspossible mediating or moderating variables, such as therapeutic alliance or type of therapeutic support.

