[44]) is a 19-item measure of therapeutic alliance, showing good psychometric properties. It comprises both positive and negative items (which are reverse-scored), and includes both a patient- and therapist-version. Statements regarding the therapeutic alliance are rated from 1 (“strongly disagree”) to 6 (“strongly agree”). A mean score is calculated by adding up all items (reverse-scoring as appropriate), calculating a mean, and then multiplying this by 19 (which should be identical to the total score if all items are completed). Thus, scores range from 19 to 114 (with higher scores indicating better alliance). It has the advantage of assessing alliance independent of symptom improvement and has been used in previous ED treatment studies (for example,
[45]).

In addition, a measure assessing healthcare use developed specifically for this study will be given (see Additional file
1). This will be administered with the standard pack of questionnaires (that is, at start-of-treatment, end-of-treatment and follow-up) for individuals who consent to the study. An estimate of cost effectiveness will be made by monitoring resource use directly associated with different treatment conditions (for example, therapist time spent providing care). The proportion of binge-free days (estimated through the EDE-Q) will also be used to estimate cost effectiveness (for example,
[46]). Therapist time will be estimated using a simple checklist of time spent engaged in treatment-related activities. The measures listed should allow comparison with other studies
[33] and also overcome some of the shortcomings in previous studies, such as limited estimates of cost-effectiveness. Self-report measures may also limit observer bias, although this may be open to subject bias. The lack of a structured clinical interview (for example, the Eating Disorder Examination) is also a shortcoming, although patients are screened on the basis of meeting criteria for an eating disorder, following an interview with an experienced clinician.

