### Sample size

A power calculation (using an α(two-tailed) of 0.05, an anticipated effect size of 1.0 and a desired power of 0.8) suggested that a minimum number of 17 individuals per group
[47], thus a minimum N of 51 is required. This was based on the findings of Ljotsson *et al*.
[19], who reported a reduction in Global EDE-Q scores during self-help treatment of 1.1 (*SD* = 0.9). Notable variability in effect sizes for GSH treatment has been reported, with a recent systematic review of self-help interventions finding an overall effect size of 0.54 (95% CIs 0.36 to 0.72) across eight studies
[33] and another
[48] citing effect sizes for the frequency of binge eating ranging from .03 to 2.68. Effect sizes in such studies have been shown to be affected by factors such as level of pathology, sample (for example, community vs. clinical), and length of follow-up
[33]. Therefore, we are aiming for a minimum N of 51, but ideally closer to 44 per group
[47] to account for this variability and to minimise the risk of the study being under-powered. Thus, a minimum overall recruitment sample of 102 is sought, estimating dropout at 50%, slightly less than the 55% reported by Loeb *et al*.
[3] and higher than the approximately 23 % reported by Ljotsson *et al*.
[19]. Attrition rate has been considered as an important factor in evaluating such trials
[48]. Therefore, in the current study, an attempt is made to more clearly define individuals who do not complete treatment, for example, noting at what point participants ceased treatment (for example,
[49]).

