### Data collection

Data from the EDE-Q provide the primary outcome variable - binge eating frequency. Secondary variables include compensatory behaviours (for example, self-induced vomiting), and ED psychopathology, as well as constructs assessed by the other measures (self-esteem, psychological distress, functional impairment). Weight and BMI are not outcome variables, but may be included in analyses, for example, to give demographic information or as covariates. Other routine demographic information (for example, ethnicity) will also be recorded. Participants are asked to complete self-report measures (mailed or otherwise given by hand) at start-of-treatment, end-of-treatment and six-month follow-up (with the exception of the HAq-II; see Table 
2). Data will be stored on a secure computer server and analysed with computer statistics software (for example, SPSS **IBM Corporation, Armonk, NY, USA**). Oxford is the lead site for data coordination. In order to promote data quality, data will be examined for impossible values and a sample of electronic data (around 10%) will be double-checked by another researcher with raw data. Blinding is not used in this study, and so an emphasis on appropriate outcome measurement and allocation concealment is crucial
[50,51].

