### Statistical methods

Regarding the primary aim - comparing active treatment and control condition - results will be analysed using analysis of variance and *t*-tests. Effect sizes will also be assessed, and expressed appropriately (for example, Cohen’s *d*). Logistic regression analyses will look at predictors of outcome, and potential mediators and moderators might also be considered. However, a number of existing studies addressing this issue have been underpowered
[33] so this remains an important consideration. Differences in outcome variables will be analysed (for example, through χ^2^, regression) to examine attrition/drop-out. In terms of cost-effectiveness, analyses will be conducted based on data obtained through the health utilisation questionnaire, therapist time questionnaire and measures of functional impairment (CIA) and ED symptoms (EDE-Q).

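### Entry allows subjective episodes alone but the primary outcome counts only objective ones, so some patients probably start at or near its floor and dilute every primary contrast

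*Protocol article*

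**What the plan says.** The Eligibility criteria section requires that participants "demonstrate regular binge eating (defined as either subjective or objective bulimic episodes) in the context of an eating disorder". None of the listed exclusions removes a patient whose episodes are all subjective, and no minimum number of objective episodes is set.

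The Primary and secondary outcomes section is narrower: "The primary outcome will be frequency of objective bulimic episodes", measured by the EDE-Q. It adds that "Comparisons will be made between pre-treatment, post-treatment and follow-up in the intervention groups". The Data collection section drops the qualifier: "Data from the EDE-Q provide the primary outcome variable - binge eating frequency".

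Under Statistical methods, "results will be analysed using analysis of variance and" *t*-tests. That section names no baseline adjustment and no analysis by episode type. The Allocation section does not stratify by episode type. The Sample size section is built "using an α(two-tailed) of 0.05, an anticipated effect size of 1.0 and a desired power of 0.8", giving 17 per group. The effect size rests on a fall in the Global EDE-Q score, not on objective-episode frequency. For the economic analysis, the Assessments and timeline section says: "The proportion of binge-free days (estimated through the EDE-Q) will also be used to estimate cost effectiveness".

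**The concern.** The entry definition and the primary outcome are both fixed in this article, and they do not match. A patient who qualifies on subjective episodes alone will probably report few or no objective episodes at baseline, so treatment can do little to lower the primary outcome for that patient.

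Two consequences follow. In each comparison with the waiting list, these patients shrink the average difference and cost power. In email versus face-to-face they act in the direction of the trial's own hypothesis. The Objectives section expects the two treatments to be comparable on binge eating frequency, and patients at the floor in both arms make them look alike whatever the treatments do for the others. If binge-free days are taken from the objective-episode item, the same patients count as largely binge-free before treatment, which weakens the cost-effectiveness measure too.

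**Working it through.** **Inputs.** From the Sample size section: two-sided α = 0.05, d = 1.0, power 0.80, 17 per group, ideally 44, dropout 50%. Not in the document, so assumed: a share p of patients with no objective episodes throughout, taken as 20% and 40%; d = 1.0 in the rest; control mean equal to the SD.

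**1. The plan's own figure.** A two-sample *t*-test with d = 1.0 needs 16.7, rounded up to 17 per group; power at 17 is 0.807. Then 17 × 3 = 51 and 51 / (1 − 0.5) = 102. The stated figures reproduce.

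**2. All patients, unadjusted, 17 per arm.** Let SD σ = 1 among patients with objective episodes, control mean μ = 1 and effect δ = 1.
- Mean difference over everyone: (1 − p)δ.
- Control variance: (1 − p)σ² + p(1 − p)μ².
- Treated variance: (1 − p)σ² + p(1 − p)(μ − δ)², where the last term is zero.
- d = difference / √(average of the two variances).

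| p | difference | variances | average | d | power at 17 |
|---|---|---|---|---|---|
| 0 | 1.00 | 1.00, 1.00 | 1.00 | 1.00 | 0.81 |
| 20% | 0.80 | 0.96, 0.80 | 0.88 | 0.80/0.938 = 0.85 | 0.67 |
| 40% | 0.60 | 0.84, 0.60 | 0.72 | 0.60/0.849 = 0.71 | 0.52 |

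A count with mean zero cannot have SD 1, so the treated arm should not be read literally. Reading the outcome as change from baseline avoids this: controls change by 0, treated patients by 1 SD, and floor patients by 0. The two variances swap arms, and the average, d and power are the same. So the dilution is also present if the ANOVA is on pre-to-post change.

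**3. Only patients with baseline objective episodes.** Expected size 17 × 0.8 = 13.6 or 17 × 0.6 = 10.2 per arm, d = 1.0: power 0.71 and 0.57. Despite fewer patients, this is about 3 points (0.708 − 0.674) and 5.5 points (0.571 − 0.516) higher.

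**4. At 44 per arm.** With d = 1.0 and the diluted values from step 2, power is 0.98 at p = 20% and 0.91 at p = 40%, so little is lost. But 44 per group is what d of about 0.6 requires: 2 × (1.96 + 0.84)² / 0.6² = 43.6. At d = 0.6, power is 0.79 with no floor patients. On the change reading, d becomes 0.48/√(0.80 + 0.5 × 0.16 × 0.36) = 0.53 at p = 20% and 0.36/√(0.60 + 0.5 × 0.24 × 0.36) = 0.45 at p = 40%, with power 0.69 and 0.55.

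**5. Email versus face-to-face.** If the true difference among patients with objective episodes is Δ, the all-patient difference is (1 − p)Δ, that is 0.8Δ or 0.6Δ.

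**6. Baseline count as covariate.** In an illustrative count simulation, adjusting for the baseline count in all patients gave power 0.78 at p = 20%, against 0.77 in the restricted analysis; at p = 40% the figures were 0.59 and 0.58. The settings are not from the protocol, so only the comparison matters: adjustment in all patients does about as well as restriction. It recovers precision but does not undo the shrinkage in step 5.

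**The case against.** Broad entry is deliberate. The abstract covers atypical variants, the Discussion calls the trial pragmatic, and the effect in all randomised patients is a legitimate target for that population. Making a subset the sole primary analysis would give that up, leave about 10 to 14 per arm at the minimum size, and rely on chance for balance, since episode type is not stratified. This stands, and it is why the fix keeps everyone in the main analysis.

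A reader might infer that patients who enter on subjective episodes start at exactly zero, cannot improve and contribute nothing. The documents do not support that. Eligibility follows a clinician's assessment while the outcome is self-reported, so a patient judged to have subjective episodes may still record objective ones on the form. A patient at zero may also develop objective episodes later, and preventing that would be a treatment effect. Such patients can improve on the secondary measures as well.

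The size is uncertain. The share p appears nowhere, and d = 1.0 comes from a different scale. The article itself cites binge-frequency effect sizes from .03 to 2.68, a spread wider than this dilution. All of that limits the numbers. Analysis sets and covariates may also be settled in an analysis plan that is not shown. None of it removes the mismatch between two definitions that the article does fix.

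**Conclusion.** The mismatch is real, and nothing in the article resolves it. Its direction is clear: weaker waiting-list contrasts, and a pull towards comparability between the two active arms. Its size is conditional. Under the assumptions in the working, power at 17 per arm falls from 0.81 to about 0.67 (p = 20%) or 0.52 (p = 40%). Those figures take floor patients to stay at zero throughout, which is the severe case. At 44 per arm the loss is small if d = 1.0 and material if d is about 0.6.

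A reader might conclude that the 17 per group was miscalculated or that the trial is shown to be underpowered. Neither follows: 17 is correct on its stated inputs, and the shortfall depends on a share the document does not give. The point is a cheap improvement worth making, not a fatal flaw.

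**What to change.** 1. In Statistical methods, replace the unadjusted *t*-tests for the primary outcome with a comparison of end-of-treatment objective-episode frequency by randomised arm, in all randomised patients, with the baseline EDE-Q objective-episode count as covariate.
2. Prespecify the same comparison in patients with at least one objective episode on the baseline EDE-Q. Apply it to objective episodes, and to binge-free days if they are taken from that item.
3. Require any conclusion that email and face-to-face are comparable to hold in that subset as well as overall.
4. In Sample size, state that 17 per group assumes patients with baseline objective episodes.
5. In Data collection, restore the word objective to the primary outcome.

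The cost is a few sentences. Table 2 already schedules the EDE-Q at baseline, so no new data are needed, and the subset is defined before treatment and compared as randomised. The downside is that the subset is smaller, is not stratified at randomisation, and gives a result that applies only to patients with objective episodes.
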